## Abstract

**Background:**

Neurogenic bowel dysfunction (NBD) is a prevalent complication among stroke patients, significantly affecting their quality of life, duration of hospitalization, medical expenses, and even mortality. Although current guidelines suggest a conservative strategy for addressing bowel dysfunction, which includes techniques such as digital rectal stimulation (DRS) and abdominal massage, the availability of interventions remains limited in healthcare facilities.

**Methods:**

This study follows a prospective randomized controlled parallel-group clinical trial design. The control group will receive standard care, while the intervention group will undergo a program that combines DRS and abdominal massage in addition to standard care. The duration of the intervention for both groups will be 6 weeks. The primary outcome measures will be the Wexner score. Furthermore, secondary outcomes measure will be assessed, including Bristol score, Patient Assessment of Constipation-Quality of Life (PAC-QoL), and Fecal Incontinence Quality of Life (FI-QoL).

**Discussion:**

This study aims to evaluate the effectiveness and safety of a bowel rehabilitation program for stroke patients with NBD. The findings will provide information that can contribute to the formulation of bowel management strategies.

**Trial registration:**

The study has been registered in the Chinese Clinical Registry under the number ChiCTR2300071709. This registration was completed on May 23, 2023. All items from the World Health Organization Trial Registration Data set are described in this manuscript.

**Supplementary Information:**

The online version contains supplementary material available at 10.1186/s13063-023-07678-2.

## Background

Lesions in the central nervous system often led to dysregulation of colon function and a lack of coordination in the anal sphincter muscles. Among these lesions, stroke accounts for the highest proportion [1]. When these lesions occur in the brain or brainstem, they can lead to delayed and prolonged transit time of feces through the colon, resulting in constipation [2]. Alternatively, patients may experience increased rectal threshold sensation, abnormal impulse conduction, fecal incontinence, or a combination of these symptoms [2, 3]. Furthermore, stroke patients may already have functional defecation disorders, including acquired dysfunction, prior to disease onset [4]. With the advancement of medicine and the clarification of pathophysiological mechanisms, the Rome Committee is progressively shifting its stance away from the term “functional.” Instead, it considers conditions such as functional constipation, functional diarrhea, or functional bloating as not independent diseases but as having the same underlying mechanisms [5]. Furthermore, Gandel [6] suggested that both functional and secondary bowel functional disorders can benefit from the same treatment strategies.

Bowel dysfunction is prevalent among stroke patients, with a reported incidence of 55.21% post-stroke and 23.96% in pre-stroke patients [7]. Among patients with bowel dysfunction, 50% take more than 30 min on average to defecate, and 70% require assistance during defecation [8]. Additionally, 15% suffer from chronic bowel dysfunction, leading to potential losses in privacy and intimate relationships and social isolation [9]. This places a significant burden of care on the patient’s family [10]. Currently, clinical caregivers heavily rely on empirical information and predominantly employ single intervention, including conservative strategies such as dietary modifications, bowel irrigation medication, or biofeedback training [11–15]. However, certain medications or enemas have the potential to harm the colonic mucosa and decrease the frequency of colonic peristalsis [16]. Surgical treatment is typically reserved for patients without rectal outlet problems who remain unresponsive to intensive medical and biofeedback therapy [13]. Nevertheless, the limited availability of medical equipment might impede patients’ access to biofeedback treatment. Hence, conservative management is recommended for NBD in stroke patients, prioritizing simple, cost-effective, minimally invasive, and reversible interventions [17].

According to guidelines, DRS is recommended as the first-line intervention and has shown a positive impact on improving bowel dysfunction in patients with spinal cord injuries [1, 18]. Moreover, abdominal massage has proven effective in reducing the severity of bowel dysfunction in elderly stroke patients [19]. The combined intervention of abdominal massage and targeted intestinal peristalsis promotion, along with DRS to facilitate fecal elimination, could potentially yield a significantly enhanced effect. However, the concurrent application of these interventions in stroke patients remains infrequent [1]. Robust evidence regarding bowel management is urgently needed. Consequently, this study aims to assess the effectiveness of a 6-week rehabilitation care program that combines DRS and abdominal massage on both bowel function and quality of life in post-stroke patients. We hypothesize that this comprehensive program will be superior to singular care interventions while minimizing complications.

## Methods/design

### Study design

This study is a single-blind, prospective, randomized controlled, parallel-group superiority trial designed to compare the effectiveness of a rehabilitation program that combines DRS with abdominal massage against the standard care provided to stroke patients with NBD.  This trial protocol uses the Standard Protocol Items: Recommendations for Interventional Trials (SPIRIT) reporting guidelines (see Additional file 1). 

### Study setting

The patient data for our study will be collected in Changsha, an area characterized by a high prevalence of stroke and associated mortality [20]. To ensure an adequate participant pool, we will implement a poster recruitment strategy at a level III hospital that houses two rehabilitation departments. These posters will contain information about the study’s objectives, duration, attention matters, and a QR code for registration. Additionally, the contact details of the study coordinator, including a telephone number, will be provided. Interested patients choose to either scan the QR code or contact the study coordinator for further information. This recruitment approach aims to effectively reach potential participants and facilitate their engagement in the study.

### Eligibility criteria

To be eligible for participation in this study, individuals must meet the following criteria: (1) age ≥ 18 years old, (2) stable phase stroke (no stroke relapses within the past 3 months), (3) awake consciousness and stable vital signs, (4) NIHSS score ≤ 15, and (5) bowel dysfunction according to the criteria of Rome IV:Constipation is defined as meeting any 2 of the following features:Difficulty with stool passage in 25% or more of bowel movements,Hard stool or lumpy consistency (Bristol Stool Form Scale type 1–2 stool) in 25% or more of bowel movements,Incomplete evacuation in 25% or more of bowel movements,Obstruction or blockage sensation in 25% or more of bowel movements,Need for digital help with 25% or more of bowel movements,Spontaneous bowel movements less than 3 times per week.Rare loose stools without the use of laxatives.Not meeting the criteria for irritable bowel syndrome.

*The symptoms of constipation must have been present for a minimum of 6 months prior to diagnosis and persisted for the preceding 3 months, in accordance with the aforementioned criteria. It is important to exclude opioid-induced constipation.

Fecal incontinence is defined as recurrent instances of uncontrolled fecal excretion.

*Patients must have experienced symptoms of fecal incontinence for a minimum duration of 6 months prior to diagnosis, with occurrences ranging from 2 to 4 times within the past week.

### Exclusion criteria

The exclusion criteria for patients are as follows: (1) severe cognitive impairment or communication difficulties; (2) history of anorectal trauma and surgery, presence of mass growth in the intestinal canal, or intestinal obstruction; (3) pre-existing condition including Crohn’s disease, inflammatory bowel disease, ulcerative colitis, or irritable bowel syndrome; (4) patients with a confirmed diagnosis of deep vein thrombosis; (5) individuals who are participating in other rehabilitation programs or clinical trials during the study period, and (6) pregnant or lactating women.

## Interventions

### Control group

The participants in the control group will be receive standard care, consisting of dietary guidance, pelvic floor muscle exercises, and skin care. In the event of no enhancement in bowel function over a span of 3 days, prescribed enemas or appropriate medications will be administered as needed.

#### Dietary guidance

Participants experiencing constipation will receive specific instructions to follow a high-fiber diet, with a recommended minimum intake of 15 g per day. However, if a high-fiber intake is not well-tolerated, a lower fiber intake will be advised. Additionally, patients will be encouraged to maintain adequate fluid intake of at least 40 ml/kg, along with an additional 500 ml per day. Moreover, patients will be instructed to schedule defecation approximately 2 h after meals and to develop a regular daily bowel habit.

For participants with fecal incontinence, the dietary recommendations entail a daily consumption of 15 g of dietary fiber. These individuals should also avoid consuming foods and beverages that can result in stool dilution or frequent bowel movements. This list comprises coffee, tobacco, alcohol, fatty foods, fructose, and lactose.

#### Pelvic floor training

The participants will be placed in a supine position, with knees bent and slightly apart. They will receive instructions to contract their anus while inhaling and simultaneously relax their thighs and abdomen muscles. The contraction should be sustained for 3–5 s, followed by a 10-s relaxation period. It is recommended to complete 10–20 repetitions per set, aiming for 4–6 sets daily.

#### Skin care

For participants with a Bristol score of 5 or 6, tampons will be used to manage fecal incontinence. When the Bristol score is 7, stool drainage procedures will be employed. To maintain the skin integrity of patients experiencing fecal incontinence, prompt cleaning of the perineum area will be conducted to ensure cleanliness and dryness. Following the cleaning process, petroleum jelly will be topically applied to the skin, followed by the application of zinc oxide ointment for skin protection.

### Experimental group

Participants in the intervention group will receive an additional intervention that includes DRS and abdominal massage, in addition to the standard care.

### Digital rectal stimulation

The procedure of DRS involves gently inserting either the middle or index finger into the anus. The rectal wall is then gently stimulated in a clockwise direction, creating a circular motion. After completing ten circles, there is a brief pause for 1–2 min. The duration of stimulation is adjusted based on various factors, including the patient’s rectal content, stool consistency, and sphincter muscle strength. The stimulation duration is set at 8 min for mild sphincter injury (anal systolic pressure 15–25 mmHg), 10 min for moderate to severe sphincter injury (anal systolic pressure 0–15 mmHg), and 15 min for severe sphincter injury (anal systolic pressure 0 mmHg). If the patient’s rectal fecal volume exceeds 100 g, the stimulation time is extended accordingly.

### Abdominal massage

Gently apply warm kneading to the acupoint RN12 (Zhongwan), RN8 (Shenque), BL26 (Guangyuan), RN3 (Zhongji), ST25 (Tianshu), and SP15 (Daheng), rubbing each acupoint for 1 to 2 min. Refer to Fig. 1 for detailed acupoint location.Perform warm pushing technique with RN8 (Shenque) as the center. Begin with a small circular motion and gradually increase the circle’s size. Then, reverse the motion from large to small circles. Warmly push the abdomen for 5 min. It is recommended to perform warm pushing from RN12 (Zhongwan) to RN3 (Zhongji), covering the sequence of the kidney meridian, stomach meridian, and spleen meridian. Apply the warm pushing technique to each part 9 to 18 times, using uniform and gentle pressure, while maintaining a slow pace. For detailed acupoint locations, see Fig. 2.Repeat the kneading technique on the acupoints RN12 (Zhongwan), RN8 (Shenque), BL26 (Guangyuan), RN3 (Zhongji), ST25 (Tianshu), and SP15 (Daheng). Knead each acupoint for 30 to 60 s.

**Fig. 1 Fig1:**
[figure not shown]
Abdominal massage acupoints

**Fig. 2 Fig2:**
[figure not shown]
Abdominal massage meridian

### Criteria for discontinuing or modifying allocated interventions

Bowel rehabilitation interventions may be discontinued due to the occurrence of adverse effects, exacerbation of health condition, or death from all causes.

### Relevant concomitant care permitted or prohibited

During the 0–6-week period of the study, participants will be instructed to refrain from participating in any other bowel rehabilitation programs. If a participant needs or seeks an alternative form of bowel rehabilitation program during the intervention phase, they will be considered ineligible for participation in the study.

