#### Sample size

The sample size calculation was performed using the PASS15 software, Version 15.0.5, with reference to a prior randomized controlled trial conducted in China that reported the Wexner score as the primary outcome [27]. We selected a significance level of 0.05 and a power of 90%. Assumptions encompassed an equal allocation of participants in a 1:1 ratio between two groups and a 20% dropout rate. The mean for group 1 (μ_1_) was 10.65, and group 2 (μ_2_) was 9.10. The standard deviation for group 1 (σ_1_) was 2.08, and for group 2 (σ2), it was 1.73. The anticipated effect size was 0.81. The sample size calculation indicated that each group should comprise 40 patients.

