## Assignment of interventions: blinding

### Who will be blinded

A third party will oversee the management and coding all data, maintaining the confidentiality of codes until the data analysis is completed. The data analyst will be blinded to the codes. The evaluation of outcomes will be performed by an assessor who is unaware to treatment allocation and has undergone training. However, it is important to note that due to the nature of bowel rehabilitation program, neither implementers of intervention nor participants can be blinded to the intervention.

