### Data collection and management

Demographic and baseline information will be collected during the initial assessment. Participants will complete a well-designed questionnaire that encompasses age, sex, height, weight, types of strokes, and medication usage. The data collection will be conducted by a staff member who is not involved in the study. Data will be collected at five time points: during screening, baseline, at post-2-week intervention, at post-6-week intervention, and at 12-week follow-up. The comprehensive data collection plan is presented in Table 1. To ensure confidentiality, each participant will be assigned a unique identifier, and all collected information will be securely stored in an electronic file. Data access will be restricted until statisticians complete the data analysis at the conclusion of the study. After a period of 3 years, all data will be deleted.

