### Statistical analyses

The collected data will undergo analysis using IBM SPSS Statistics 25.0 (IBM Corp., Armonk, NY, USA). Baseline characteristics will be summarized using descriptive statistics. Continuous variables, such as the Wexner score and quality of life score, will be reported using means, medians, standard deviations, and score ranges. Categorical valuable, such as BSFS, will be reported as counts and percentages. To ascertain normality, the Kolmogorov-Smirnova test will be applied. In instances of normally distributed data, independent samples *t*-test will be employed to compare efficacy between the intervention and control groups in terms of the Wexner score, PAC-QoL, and FI-QoL. Non-normally distributed data will be analyzed using the Wilcoxon rank sum test with a test statistic of *Z*. For assessing changes across distinct time points, we will employ repeated measures ANOVA. The chi-squared test will be used to analyze categorical data for the BSFS. A *p*-value < 0.05 will be considered statistically significant. We will perform an intention to treat analysis for participants who either lack adherence to bowel care (defined as comply with less than 80% of bowel care) or discontinue the study. These participants will be retained within their originally randomized treatment arm for analysis. Addressing missing data, a multiple imputation method will be implemented. No supplementary analyses will be carried out in this study, and the study design does not encompass interim analyses.

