### Plans for communicating important protocol amendments to relevant parties (e.g., trial participants, ethical committees)

The principal investigator will oversee protocol modifications. Any updated protocols will be promptly reported to the Chinese Clinical Trial Registry, institutional review board (IRB), and all other trial participants and clinical personnel.

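### The concomitant-care rule makes randomised participants ineligible if they need or seek another bowel programme, which would probably forgo their later outcomes on a trigger plausibly tied to poor response

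*Protocol article*

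**What the plan says.** Under Relevant concomitant care permitted or prohibited, participants are told not to join other bowel rehabilitation programmes in weeks 0 to 6. Of anyone who needs or seeks one in that period, the article says "they will be considered ineligible for participation in the study". Stopping the allocated intervention is covered in a separate section (Criteria for discontinuing or modifying allocated interventions), which lists adverse effects, worsening health and death.

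Statistical analyses applies intention to treat to those who adhere poorly or discontinue the study: "These participants will be retained within their originally randomized treatment arm for analysis". It adds: "Addressing missing data, a multiple imputation method will be implemented". Outcomes after baseline are due "at post-2-week intervention, at post-6-week intervention, and at 12-week follow-up" (Data collection and management). On blinding, "neither implementers of intervention nor participants can be blinded to the intervention".

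Three other places bear on the point:
- Exclusion criterion (5) bars people who take part in other rehabilitation programmes or trials during the study period.
- Control group provides that, if bowel function has not improved over 3 days, "prescribed enemas or appropriate medications will be administered as needed".
- Provision for post-trial care says that controls who show a need for the intervention during the study will be offered it.

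**The concern.** Eligibility is settled before randomisation, but this rule applies an eligibility term afterwards. It covers participation in the study and not only the allocated care. Need alone triggers it; no other programme has to be taken up. In a trial of bowel function, needing something more is plausibly a sign that the allocated care is not working.

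If a site follows the sentence literally, it stops seeing the participant, and the week-6 and week-12 scores are never collected. The intention-to-treat rule settles who is analysed, and imputation fills the gap, but neither recovers what happened. Standard imputation removes the bias when leaving depends only on scores already recorded at baseline or week 2. It does not fully do so for someone who worsens between weeks 2 and 6. Because participants know their arm and controls receive standard care only, loss could be uneven between arms. If more poor responders leave the control arm, the remaining controls look better than they should and the bias runs against the intervention. If more leave the intervention arm, it runs in its favour.

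**Working it through.** **Inputs from Sample size.** Means 10.65 and 9.10, SDs 2.08 and 1.73, significance level 0.05, power 90%, 20% dropout, 40 per group. Group 1 is taken to be control, since a higher Wexner score is worse. Scores are assumed normal, and the comparison is taken at week 6.

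**The plan's own figure.** The planned difference is 10.65 − 9.10 = 1.55. The pooled SD is √((2.08² + 1.73²)/2) = 1.913, and 1.55/1.913 = 0.81, as stated. With a two-sided test, n = 2(1.960 + 1.282)² × 1.913²/1.55² ≈ 32.0, or 33 after rounding up. Then 32/0.8 = 40 and 33 × 1.2 = 39.6, so the stated 40 reproduces (33/0.8 would give 42). The dropout allowance covers loss of numbers, not bias.

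**Assumed, not in the documents.** The share lost, how strongly leaving relates to the score, and the correlation between week-2 and week-6 scores (0.3, 0.5 or 0.7).

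**Step 1: before imputation, moderate case.** If a fraction f of an arm leaves and leavers average k SD worse than the arm mean, the mean of those remaining shifts by f·k·SD/(1 − f). For 10% of controls only:
- k = 0.5: 0.1 × 0.5 × 2.08/0.9 = 0.12, so the difference falls to 1.43.
- k = 1: 0.1 × 1 × 2.08/0.9 = 0.23, so the difference falls to 1.32.

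**Step 2: before imputation, worst tail.** If exactly the worst p leave, the shift is φ(z)/(1 − p) SD. At p = 0.10 that is 0.1755/0.90 = 0.195 SD.
- Controls only: 0.195 × 2.08 = 0.41 (26% of 1.55).
- Both arms equally: 0.195 × (2.08 − 1.73) = 0.07 (4%).

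Leavers here average 1.75 SD worse than their arm, so this is close to an upper bound.

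**Step 3: after imputation.** Week 6 is regressed on week 2 among those observed, which gives the expected value of regression-based multiple imputation with week 2 as the only predictor. This was simulated with 10% missing in an affected arm. The residual in SD units is multiplied by 2.08 for controls only, or by 0.35 when both arms lose equally. For the moderate rows, leaving follows a logistic model in the week-6 score with slope 0.5 or 1 per SD, so that leavers average 0.44 or 0.82 SD worse. The 5% share in the unequal row has its own residual, multiplied by 1.73 and subtracted.

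| Leaving depends on | Share lost | Residual bias (points) | % of 1.55 |
|---|---|---|---|
| Week-2 score only | 10% of controls | 0.00 | 0 |
| Week-6 score, moderately | 10% of controls | 0.05 to 0.17 | 3 to 11 |
| Week-6 score, moderately | 10% of controls, 5% of intervention | 0.03 to 0.10 | 2 to 6 |
| Week-6 score, moderately | 10% of both arms | at most 0.03 | at most 2 |
| Week-6 score, exact worst tail | 10% of controls | 0.38, 0.33, 0.24 | 24, 21, 16 |
| Week-6 score, exact worst tail | 10% of both arms | 0.06, 0.06, 0.04 | 4, 4, 3 |

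The three values in the worst-tail rows are for correlations 0.3, 0.5 and 0.7. Their residuals are 0.182, 0.158 and 0.116 SD; for example, 0.182 × 2.08 = 0.38.

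**The case against.** The loss of outcomes is inferred. No sentence says that assessments stop, the article plans diaries, compensation and phone reminders to complete follow-up, and a fuller protocol is said to exist. This stands, and it is why the consequence is put as probable. It does not remove the point, because the sentence as printed ends participation and nothing in the article reconciles it with the intention-to-treat rule.

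A reader might infer something stronger: that these participants are dropped from the analysis, in breach of intention to treat. The documents do not support that. Statistical analyses can be read as covering them as people who discontinue the study, and no passage takes a randomised participant out of the analysis.

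Loss may also be rare. Rescue enemas or medication are available, and controls in need may be offered the trial intervention, although that provision sits under post-trial care and its timing is unclear. Both make a loss confined to controls less likely. That scenario also biases against the intervention, which is conservative for a superiority claim. These arguments bear on size and are reflected in the range given.

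Finally, the computed bias is relative to the score a leaver would have had without another programme. Continued follow-up records the score after any such programme, so for those who take one up it does not recover that quantity. The gain is clear for those who need or seek a programme but never start one. For the others, what is gained is an observed outcome under the intention-to-treat comparison the protocol already chose.

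**Conclusion.** The point holds as a badly fixed rule. A post-randomisation event plausibly linked to poor response ends participation, and would probably create missing week-6 and week-12 outcomes that need not be missing. The planned analysis limits the damage but leaves it resting on an assumption that the trial's data cannot test.

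The size cannot be derived from the documents. For an assumed 10% loss in controls only, the residual bias is about 0.05 to 0.17 points (3% to 11% of the planned difference) if leaving is moderately related to the week-6 score. The 0.24 to 0.38 points of the worst-tail case is an extreme and should not be read as the expected bias. With equal loss, or loss driven only by the week-2 score, the bias is close to zero. All of this assumes normal scores, group 1 as control, and imputation from week 2 alone. The change is worth making because it is cheap and uncollected outcomes cannot be recovered later, not because a large bias has been shown.

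**What to change.** Replace the ineligibility sentence under Relevant concomitant care permitted or prohibited with:

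*A participant who needs or seeks another bowel rehabilitation programme after randomisation may stop the allocated care but remains in follow-up at weeks 2, 6 and 12 and is analysed in the randomised arm under intention to treat. The date and type of any other programme actually taken up, including trial intervention given to a control under the post-trial care provision, are recorded as a protocol deviation.*

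Also state that exclusion criterion (5) applies at enrolment only; otherwise the eligibility conflict remains for anyone who takes up another programme.

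The cost is one replaced sentence, one clarification and one case report form field, with no change to sample size or visits. Recruitment began on 1 June 2023, so this is an amendment, and the route is in place: "Any updated protocols will be promptly reported to the Chinese Clinical Trial Registry", as well as to the IRB. The downside is some dilution of the contrast among those who take up another programme, because the estimate is then a treatment-policy one.
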